### Participant timeline {13}

The participant timeline is shown in Fig. 1.

**Fig. 1 Fig1:**
[figure not shown]
Schedule of enrolment, interventions, and assessments (AA, air ambulance)

### Sample size {14}

The trial will use a group sequential, superiority design and one interim analysis with O’Brien Fleming stopping boundaries, to inform early stopping for harm or benefit. Using data from the red cell and plasma (RCP) study [4], the composite endpoint of 24-h mortality or massive transfusion (defined as the total blood components given being greater than or equal to 10 units) in the first 24 h was calculated as 68%. We have therefore used a baseline event rate of 68% in our calculations.

Several studies have reported that WB transfusion versus blood components (or addition of platelets to RBC and plasma resuscitation) are likely to reduce mortality and overall transfusion, hence the reason for choosing this composite outcome. Williams [16] reported that a similar number of units were received in ED, although fewer units of RBC, plasma, and overall products after leaving ED (the median (IQR) were 0 (0–4) for WB and 3 (0–10) for traditional component therapy). Spinella [21] reported a 24-h mortality rate of 4% in WB vs 12% in component therapy (67% relative difference and 8% absolute difference). A higher chance of massive transfusion in WB compared to component therapy (89% vs 78%) though differences were expected as the groups were determined by the blood products transfused. A sub-study of the Pragmatic, Randomized Optimal Platelet and Plasma Ratios (PROPPR) trial [22] showed an 11% absolute (66% relative difference) in 24-h mortality between those patients who did and did not received platelets. Perkins [23] reported a significant reduction in blood product use at 24 h in the WB group. The RCT of WB versus components showed similar results, but only in a sub-group analysis of patients without severe brain injury (median [IQR] 24-h total transfusion was 11 units [5, 17] vs. 16 units [4,41], *p* = 0.02) [23].

Hence, combining all the evidence above, we have powered the study to detect a 12% absolute (38% relative) difference in the composite endpoint between the two treatment arms (68% vs 56%). A two-sided test with 85% power, 5% type I error, 1-1 allocation, and one interim analysis would require 602 participants. After allowing for 25% of participants being in traumatic cardiac arrest and an additional 5% drop out, the total number of participants required for this trial is 848.

### Recruitment {15}

A national survey of pre-hospital practice, conducted in 2020 [12], and the red cell and plasma study conducted in England [4] were key to estimating the number of patients per year receiving blood transfusion delivered by each participating air ambulance.

The air ambulances taking part in the study will carry a trial intervention box containing blood products (either WB or standard care), and when they identify a patient requiring pre-hospital blood transfusion, they will open the box and administer the blood products. This should ensure that if a patient requires a blood transfusion and is attended by a participating air ambulance service, they are recruited into the trial.

## Assignment of interventions: allocation

### Sequence generation {16a}

A restricted randomisation method will be used in this trial. It will consist of randomly permuted blocks of varying undisclosed sizes, and stratified by AAS, to account for variation in trauma care and type of trauma between delivery sites. There will be a 1:1 allocation ratio, to the intervention and control arms. The allocation sequence will be produced from a specification provided by the trial statistician to Sealed Envelope (a centralised web-based randomisation service) and quality checked by the trial statistician.

### Concealment mechanism {16b}

Allocation will be conducted by the participating transfusion laboratory teams using Sealed Envelope, a centralised web-based randomisation service. Only Sealed Envelope and the trial statisticians will have access to the randomisation list.

### Implementation {16c}

On randomisation, an email notification will be sent to the transfusion laboratory team and NHSBT CTU, which will include the randomisation number, date and time of randomisation, and the allocated treatment (whole blood or standard care). The randomisation number must be added to the trial box and will be used on all subsequent study documentation.

Using the randomised allocation, boxes of blood components will be prepared by the participating transfusion laboratory teams. Transfusion laboratories will be supplied with pre-printed ‘SWiFT randomisation number’ labels to which they will add by hand the randomisation number. A registered user at the transfusion laboratories will perform a unique randomisation for each box to be used by the AAS. The allocated trial intervention will be packed into transport boxes, ensuring that the randomisation number is clearly documented on the outside of the box. The packed, sealed transport boxes will be dispatched to the AAS using an established courier service as required for each site. Unused boxes should be returned to the transfusion laboratory and if unopened replaced “like-for-like”. A new randomisation will only be performed once the box has been used (i.e. contents have been transfused to a participant) or if the box has been returned opened but the contents were not used.

## Assignment of interventions: blinding

### Who will be blinded {17a}

The AAS clinical teams will be blinded to the randomised allocation until the trial box is opened, after which point it is not feasible to maintain blinding. To ensure that the team can remain blinded until the box is opened, the boxes containing intervention or control will be the same size and shape. It is not possible to blind the team at the receiving hospital to the intervention.

Participants will be blinded to allocation until the trial box is opened, but they may discover this information post-randomisation (e.g. by reading their medical notes or requesting this information from the Research Team), although there is no obligation to inform the participant which treatment they received.

### Procedure for unblinding if needed {17b}

Not applicable. Unblinding will effectively occur when the trial box is opened.

## Data collection and management

### Plans for assessment and collection of outcomes {18a}

On arrival at hospital, the AAS clinical team will hand over clinical responsibility for the participant to the receiving hospital team and complete the pre-hospital form (on the eCRF). Each unit of blood administered pre-hospital will be recorded on the eCRF, along with the donation number (G number) of the unit and the transfusion start time.

The principal investigator and research team at the receiving hospital will be responsible for collecting the clinical data for trial participants.

The transfusion laboratory at the receiving hospital will be responsible for recording the final ‘fate’ of all blood components that were administered to the participant, to ensure full traceability.

Data to be collected by the research team at 24 h post-randomisation include the following: participant demographics and baseline data, participant status (alive/dead) at 6 h and 24 h, total number of blood components transfused, cell salvage/autologous blood transfusion, and any haemostatic agents received.

Data to be collected by the research team at 30 days post-randomisation include participant status (alive/dead), total number of blood components transfused, critical care unit admission (yes/no), plus date/time of admission where applicable, hospital resource use (up to discharge from acute care hospital or death, whichever is first), thromboembolic events (clinically diagnosed), and any transfusion reactions which have been reported to SHOT (occurring in first 14 days post-randomisation).

For participants that are alive at 90 days post-randomisation, data collected will include participant status (alive/dead), health-related quality of life questionnaire (EQ-5D-5L, or EuroQol 5 Dimension Youth, EQ-5D-Y for participants aged 5–14 years), and health, social, and wider care service use questionnaire. Limited patient identifiable information will be collected to enable linkage to the Trauma Audit and Research Network (TARN) and Intensive Care National Audit and Research Centre (ICNARC) routinely collected data. This will prevent duplicate data collection and reduce the burden of data collection for hospital research teams.

### Plans to promote participant retention and complete follow-up {18b}

With the exception of cases where consent is withdrawn, there are no other specific circumstances where a participant should be withdrawn from the trial. If a participant is withdrawn, a withdrawal form will be completed which will detail the reason for withdrawal, including whether we are able to use the data already collected.

### Data management {19}

The principal investigator has overall responsibility for data collection at each site. Participant data will be entered onto the trial database, which was designed and will be administered by the NHSBT Clinical Trials Unit Data Management team using OpenClinica. The OpenClinica database will be used for electronic data capture (EDC) management and reporting on this trial. Training and instructions for completion of eCRFs will be given to each site during at site activation.

All case report forms will be electronic. The eCRFs will be completed directly onto the EDC system (i.e. the database).

The NHSBT CTU staff will be in regular contact with local site personnel to check on progress and to help with any queries that may arise. Incoming electronic forms will be checked for completeness, consistency, timelines, and compliance with the protocol.

Direct access to eCRF data will be granted to authorised representatives from the sponsor, NHSBT CTU, host institution, and the regulatory authorities to permit trial-related monitoring, audits, and inspections in line with participant consent.

### Confidentiality {27}

Direct access to eCRF data will only be granted to authorised representatives from the sponsor, NHSBT CTU, host institution, and the regulatory authorities to permit trial-related monitoring, audits, and inspections in line with participant consent. Each participant will be allocated an individual trial identification number.

### Plans for collection, laboratory evaluation, and storage of biological specimens for genetic or molecular analysis in this trial/future use {33}

SWiFT participants will be eligible for enrolment in the ACIT-2 study at sites that are recruiting patients to that study. The details of the collection and analysis of the samples taken will be according to the ACIT-2 study protocol.

## Statistical methods

### Statistical methods for primary and secondary outcomes {20a}

Analyses will be described in detail in a full statistical analysis plan (SAP). This section summarises the main points.

The following factors will be used to assess baseline comparability of the randomised groups:
◦ Age in years, reported as a median (IQR)◦ Number and proportion of paediatric participants (defined as < 16 years)◦ Sex (male or female)◦ Type of injury (blunt or penetrating)◦ Nature of traumatic injury (high or low energy transfer)◦ Injury Severity Score, reported as a median (IQR), defined as the sum of the squares of the highest AIS grade in each of the three most severely injured areas. Note if the participant is dead upon arrival to hospital, then the ISS is not calculated and hence will be assumed to be 75 (the maximum score) [24].◦ Systolic blood pressure (mm Hg), reported as a median (IQR)◦ Heart rate (per minute), reported as a median (IQR)◦ Glasgow Coma Scale, reported as a median (IQR). This score measures eye opening, verbal and motor response functions◦ Age of blood in days, reported as a median (IQR). This will be determined using routinely collected NHSBT data.

A CONSORT diagram will be produced to show the flow of participants through the trial.

#### Primary outcome

The primary outcome will be determined as the proportion of participants who have either died (from all causes) or received 10 or more units of blood components, within the 24 h from randomisation (a participant is considered randomised and entered into the trial when the trial intervention box has been opened). The following will be included in the blood component count: RBC, platelets, whole blood, thawed plasma (or LyoPlas), and cryoprecipitate. In this trial, for the purposes of analysis, two units of whole blood will be counted as equivalent to four total units due to the volume difference between the intervention and control arm, the fact that two units of whole blood contain the equivalent of two units of plasma plus two units of packed RBCs, and for the massive transfusion part of the primary analysis, both arms will start will an equal baseline. The composite outcome will be analysed using a mixed logistic regression model with adjustment for AAS, fitted as a random effect. A superiority hypothesis will be tested and the results from the adjusted analysis will be considered the primary analysis.

All analyses will be performed on a modified intention to treat basis, to exclude participants who experience a traumatic cardiac arrest, but will include all other randomised patients on whom a value of the response variable has been obtained, including those randomised in error and regardless of the participants’ adherence to the protocol. The data will be presented and analysed according to the arm to which the participant was randomised, regardless of whether they received the randomised intervention or not.

The primary outcome will be replicated per protocol, which will exclude participants who experience a traumatic cardiac arrest, those who experience a protocol deviation, were randomised in error or were withdrawn from the trial. The data will be presented and analysed according to the arm to which the participant was randomised.

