### Methods for additional analyses (e.g. subgroup analyses) {20b}

The primary outcome analysis will be replicated for four subgroups:Presence of a traumatic brain injury defined as Abbreviated Injury Scale head score 3 or aboveAdult vs paediatric (< 16 years)Blunt vs penetrating traumatic injuryInjury Severity Score: ≤ 15 vs 16–25 vs ≥ 26

The last two of these subgroups have been added to allow comparison to previous trials.

We are interested in how the following factors are associated with the primary outcome. However, as these factors occur after randomisation and are not baseline characteristics, they cannot be subgroup analyses. Instead, each factor will be presented by treatment arm for the primary outcome. Then, each factor will be separately fitted in the primary outcome model to assess if the factor is significantly associated with the primary outcome after the other risk adjustment and how it affects the treatment effect. For the age of whole blood, only those in the intervention arm will be included, and hence, the data will just be tabulated by level of the factor against the primary outcome, and the treatment effect will not be explored.Anaesthetised pre-hospital or notTransport time to hospital: ≤ 20 min vs > 20 minAge of whole blood: age of units of whole blood in days categorized into young (1–14 days) and old (> 14 days)

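### The primary model adjusts only for air ambulance service and forgoes the precision that patient-level baseline variables already listed in the protocol could add

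*Protocol article*

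**What the plan says.** Under Primary outcome in the statistical methods, the composite is to be analysed with a "mixed logistic regression model with adjustment for AAS, fitted as a random effect", and the result of that adjusted analysis is declared primary. AAS is also the only stratification factor in the randomisation (Sequence generation). No patient-level covariate is named.

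The section on statistical methods for primary and secondary outcomes {20a} lists age, sex, injury type, energy transfer, Injury Severity Score (ISS), systolic blood pressure, heart rate and Glasgow Coma Scale, together with age of blood. Their stated role is this: "The following factors will be used to assess baseline comparability of the randomised groups". ISS is set to 75 for anyone dead on arrival at hospital.

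The section on additional analyses {20b} plans to add certain post-randomisation factors to the primary model one at a time, to see whether each is "significantly associated with the primary outcome after the other risk adjustment". It does not say what that other adjustment is.

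On sample size: "We have therefore used a baseline event rate of 68% in our calculations", against 56% with whole blood. "A two-sided test with 85% power, 5% type I error, 1-1 allocation, and one interim analysis would require 602 participants". Allowance for traumatic cardiac arrest and drop-out brings the total to 848.

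**The concern.** Adjusting for AAS removes differences between services. It does nothing about differences in age, physiology or injury mechanism between patients treated by the same service. If such variables predict 24-hour death or massive transfusion, leaving them out makes the treatment estimate less precise than the same data allow. A chance imbalance in severity would then appear in the comparability table with no pre-specified way to account for it.

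The choice is stated outright, so an analysis plan that follows the article inherits it. At stake is some power and a narrower confidence interval, obtainable without recruiting anyone further.

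**Working it through.** **Inputs.** From Sample size {14}: control risk 0.68, intervention risk 0.56, two-sided 5%, 85% power, 602 evaluable (301 per arm), one O'Brien–Fleming interim, 25% cardiac arrest and 5% drop-out. From Interim analyses {21b}: interim at 400, an information fraction of 400/602 = 0.664. Assumed, because the document gives no figure: how well the covariates predict the outcome.

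**Step 1: the plan's own figures.**
- The usual two-proportion formula gives 293 per arm, or 586. The two-look inflation at fraction 0.664 is 1.016, so 586 × 1.016 ≈ 595.
- On the log-odds scale, which suits a logistic test, n per arm = (1.960 + 1.036)² × [1/(0.68 × 0.32) + 1/(0.56 × 0.44)] / (ln 0.599)² ≈ 295.7. With inflation the total is about 601 to 602, in agreement with the stated 602.
- Losses: 602/(0.75 × 0.95) ≈ 845, within 0.4% of 848.

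**Step 2: power without patient covariates.** SE of the risk difference = √[(0.68 × 0.32 + 0.56 × 0.44)/301] = 0.0393. Power = Φ(0.12/0.0393 − 1.96) = 86.4%. This ignores the interim, whose effect is small and common to all rows below.

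**Step 3: power if covariates explain a share R² of outcome variance.** The SE is multiplied by √(1 − R²), which is worth the same as an unadjusted trial of 602/(1 − R²).

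| Assumed R² | Power | Equivalent unadjusted N |
|---|---|---|
| 0 | 86.4% | 602 |
| 10% | 89.6% | 669 |
| 20% | 92.7% | 752 |

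**Step 4: simulated logistic models.** The settings were N = 602, marginal risks 68% and 56%, one normally distributed covariate, fixed design, no AAS effect and 3,000 trials per row (Monte Carlo error about 0.6 points). Both tests were run on the same simulated trials.

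| Covariate AUC, control arm | Power unadjusted | Power adjusted | Conditional odds ratio | SE of standardised risk difference |
|---|---|---|---|---|
| 0.50 | 85.4% | 85.7% | 0.599 | 0.0393 |
| 0.64 | 87.0% | 89.0% | 0.582 | 0.0378 |
| 0.74 | 84.9% | 90.3% | 0.540 | 0.0369 |
| 0.82 | 87.1% | 94.7% | 0.488 | 0.0337 |

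Within rows the gain runs from about 0 to 8 points (up to 9 if the last row is set against a nominal 86%). The standardised risk difference averages about −0.12 in every row. A covariate with no predictive value costs practically nothing. Since AAS is already in the planned model, the R² that counts is what the covariates explain beyond AAS.

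**The case against.** The AAS-only model is sound. It reflects the sole stratification factor, and the trial reaches its 85% target without covariates, so the added power is a bonus forgone and not a shortfall. No figure in the article shows that the listed variables predict strongly, and it states neither when they are measured nor how complete they are. The remedy also takes some work: patients of any age are eligible, and normal blood pressure and heart rate change with age. All of this stands, and it limits the point to an improvement.

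A reader might go further in three ways that the document does not support.

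- *That the model yields only an odds ratio and so cannot estimate the 12-point difference the trial is powered on.* The article names no effect measure for the primary result, and that choice is commonly left to the analysis plan. The design risks correspond to an odds ratio of (0.56/0.44)/(0.68/0.32) = 0.599 and a risk ratio of 0.56/0.68 = 0.824, which do differ. But a logistic test addresses the same null hypothesis as a comparison of proportions, the log-odds formula returns the stated 602, and a risk difference can be standardised from the same fit.
- *That the cost-effectiveness ratio is compromised.* The secondary outcome section gives the economic evaluation its own regression and bootstrap methods and a separate analysis plan.
- *That the additional-analyses section contradicts the primary model.* Its reference to other risk adjustment may simply mean AAS. It is an ambiguity of wording.

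**Conclusion.** The point holds as one of efficiency: a stated choice leaves baseline information unused in the primary model. It does not invalidate the analysis, reveals no sample-size error, and shows no mismatch between the design and the effect scale.

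Its size depends wholly on an assumption. Power moves from about 86% to about 90% or 93% at an R² of 10% or 20%. The simulated range starts at essentially no gain and reaches roughly 8 to 9 points only with a covariate of AUC 0.82. The calculations take the design risks as true, treat the design as fixed and set the AAS effect to zero. The change is still worth making, because its expected benefit is positive and its cost is small if it is settled in time.

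**What to change.** - Amend the primary outcome paragraph to add fixed effects for age, injury type (blunt or penetrating), systolic blood pressure, heart rate and Glasgow Coma Scale to the AAS random effect. Use only values recorded before the box is opened, since the article defines that as randomisation.
- State the functional form of age and the vital signs in advance, allowing for children and adults in one model.
- Give a simple imputation rule for missing baseline values, so that nobody is dropped.
- Exclude ISS, because the value of 75 assigned to those dead on arrival makes it partly a record of the outcome.
- Keep the AAS-only model as a sensitivity analysis.
- In the additional-analyses section, replace the reference to other risk adjustment with the covariates actually in the final model.
- Fix all of this before anyone choosing covariates has seen outcome data by arm. The data monitoring section gives the trial statisticians such access while the trial is running.

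As an option only, report a standardised risk difference from the same model. It stays at about 12 points whichever covariates are included, whereas the conditional odds ratio shifts (0.599 to 0.488 in the simulations).

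The cost is protocol and analysis-plan wording and a few modelling and imputation decisions. No new data collection is foreseen, provided the listed variables are recorded before box opening, which the article does not state.

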### Outcomes {12}

The primary outcome is the proportion of participants who have died (all-cause mortality) or received massive transfusion in the first 24 h from randomisation. A participant is considered randomised and entered into the trial when the trial intervention box has been opened.

For the purposes of analysis, two units of whole blood will be counted as equivalent to four total units due to the volume difference between the intervention and control arm, the fact that two units of whole blood contain the equivalent of two units of plasma plus two units of packed RBCs, and for the massive transfusion part of the primary analysis, both arms will start will an equal baseline.

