#### Secondary outcome analysis

All-cause mortality at 6 h, 24 h, 30 days, and 90 days, the proportion of participants who receive 10 or more units of any blood components, and presence of coagulopathy will each be analysed separately using the same model that is described for the primary outcome.

Organ failure-free days and days in critical care and an acute care hospital will be reported as a median and IQR, by treatment arm and overall.

Units of each blood component received in the 24 h after randomisation will be summarised with a median and interquartile range and analysed using a negative binomial model, with adjustment for AAS.

Amount of millilitres (ml) of cell salvage at 24 h after randomisation and lactate, base excess, and pH level in first sample taken on arrival at acute care hospital will be analysed separately using a mixed linear regression model, with adjustment for AAS.

For each of the additional haemostatic agents, the number of participants who received each agent will be presented by trial arm and overall.

Thrombosis (arterial or venous thrombosis) up to 30 days after randomisation (or death or hospital discharge, whichever is first) and transfusion reactions/events relating to pre-hospital blood components which have been reported to SHOT (Serious Hazards of Transfusion) occurring in the first 14 days after randomisation will be summarised.

The economic evaluation will establish the resources required to provide the whole blood intervention, estimate intervention as compared to standard care costs, and conduct a full incremental cost-effectiveness analysis. Analyses will be undertaken against a primary perspective of the NHS/Social Care. Cost and outcome data will be synthesised to present incremental cost-effectiveness ratios for the primary outcome and cost per quality-adjusted life-year at 90 days. Multivariable regression analyses and bootstrapping will be employed, uncertainty will be explored, and cost-effectiveness acceptability curves will be presented. The internationally recognised CHEERs guidelines will be followed, and planned analyses will be described in a health economics analysis plan, which will be fully concordant with the SAP.

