The choice of the comparator arm represents current pre-hospital transfusion practice in England. Therefore, the main differences between the intervention and standard care arms are the addition of platelets in WB, and the fact that the WB transfusion is logistically easier and faster to administer than component therapy. We are not aware of any trials that have assessed the addition of platelets to RBC and/or plasma resuscitation in the pre-hospital setting, thus making this trial unique. A sub-study of the PROPRR trial in the hospital setting suggested that trauma patients who received early platelets had an 11% reduction in 24 h and 30-day mortality [22]. In the case of WB, platelets are cold-stored (unlike routine platelets that are stored at room temperature), and in vitro data have shown that platelet count declines in the WB during storage; however, platelets become more activated [18, 24, 26]. Therefore, it could be argued that activated platelets could be more effective in promoting haemostasis and rapidly stopping bleeding, although this may be associated with increased thrombotic risks, all of which will be assessed in this trial.

Observational studies have suggested survival benefits with WB transfusion versus component therapy (mostly at 24 h), with only one study reporting mortality benefit at 30 days (odds ratio 2.19; 95% CI 1.01–4.76; *p* = 0.047) [16, 21, 23]. Three observational studies reported no difference in 30-day mortality (*n* = 830), while one study (*n* = 354) showed a 13% decrease in 30-day mortality with WB transfusion (*p* = 0.002) compared with component therapy [13]. This reported an 8% absolute difference in 24-h mortality between WB (4%) vs component therapy (12%); it also showed a higher proportion of patients receiving massive transfusion in the WB group compared to component therapy (89% vs 78%).

Although there is some evidence of benefit with the use of WB, there have been no prospective randomised trials exploring the clinical and cost effectiveness of pre-hospital administration of WB versus component therapy for bleeding trauma patients. The optimal pre-hospital transfusion strategy has yet to be established and transfusion practice varies across the country. Therefore, it is essential for patients, healthcare professionals, and blood services that the clinical and cost effectiveness of pre-hospital WB transfusion is evaluated in a large trial before its widespread implementation in routine practice.

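### The modified ITT rule covers all analyses, so as written the by-arm summaries of thrombosis and transfusion reactions leave out participants in traumatic cardiac arrest, planned at about a quarter of those randomised

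*Protocol article*

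**What the plan says.** The protocol article fixes the analysis population under Primary outcome: "All analyses will be performed on a modified intention to treat basis". That basis leaves out anyone who has a traumatic cardiac arrest. The same paragraph has the data analysed "according to the arm to which the participant was randomised, regardless of whether they received the randomised intervention or not". The only other population described is the per-protocol set. That set is limited to the primary outcome and also removes arrests.

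Secondary outcome analysis lists "Thrombosis (arterial or venous thrombosis) up to 30 days after randomisation" and the reactions reported to the national haemovigilance scheme within 14 days. Both are to be summarised, and neither is given a population.

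Three other places bear on who is affected:

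- **Entry to the trial.** Outcomes {12} states: "A participant is considered randomised and entered into the trial when the trial intervention box has been opened". Eligibility criteria {10} do not exclude patients in arrest.
- **Expected share.** Sample size {14} gives a planned total of 848 and expects a quarter of these participants to be in arrest.
- **Purpose.** Safety is among the secondary objectives in Objectives {7}. The Discussion says of activated platelets in whole blood: "although this may be associated with increased thrombotic risks, all of which will be assessed in this trial".

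**The concern.** Excluding arrest patients from the efficacy comparison is a design choice that the sample size already allows for. Safety asks a different question, namely what happened to the people who were given the product. A patient in arrest who is transfused from a trial box is exposed to it like anyone else.

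A SAP that follows the article to the letter would leave these patients out of the by-arm tables of thrombosis and transfusion reactions. The comparative safety result would then describe a narrower group than the one treated. It would also be less able to show or bound uncommon harms, in a trial that names thrombosis as a possible harm of the intervention and undertakes to assess it.

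**Working it through.** **1. The plan's own sample size.** Inputs from Sample size {14}: 68% vs 56%, two-sided 5%, 85% power, 1:1 allocation, one O'Brien-Fleming interim. The plan states: "A two-sided test with 85% power, 5% type I error, 1-1 allocation, and one interim analysis would require 602 participants".

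- Fixed design, pooled variance: 293 per arm, 586 in total.
- Inflation for one interim: 1.007 at half information, giving 590, and 1.016 at 400/602 of the information, giving 595.
- The stated 602 is within 3% of these.
- Total: 602 / 0.75 / 0.95 = 845, against 848 stated. In reverse, 848 × 0.75 × 0.95 = 604.

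The sample size reproduces. The check also shows that the 25% is a share of all randomised participants, meaning those whose box was opened.

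**2. Number removed by the rule.** 848 × 0.25 = 212, about 106 per arm. This leaves 848 − 212 = 636, or 318 per arm instead of 424.

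**3. Effect on what a zero-event result can exclude.** The one-sided 95% upper bound after no events in n participants is 1 − 0.05^(1/n).

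| Participants per arm | Upper bound |
|---|---|
| 424 (all exposed, arrests included) | 0.70% |
| 371 (assumption: half of the arrest participants transfused, 318 + 53) | 0.80% |
| 318 (arrests excluded) | 0.94% |

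All rows assume that every non-arrest participant was transfused. The article gives no exposure rate for either group.

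**4. Chance of seeing at least one event in an arm**, 1 − (1 − p)^n. The true rates p are assumptions and are not in the article.

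| p | n = 424 | n = 318 |
|---|---|---|
| 0.5% | 88.1% | 79.7% |
| 1% | 98.6% | 95.9% |
| 2% | 99.98% | 99.84% |

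The loss matters only for uncommon events.

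**5. Does any other section release safety from the rule?**

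- Plans for assessment and collection of outcomes {18a} collects thromboembolic events and haemovigilance reports without an arrest exclusion, so the data will exist.
- Adverse event reporting and harms {22} requires reporting of serious events related to the pre-hospital components, again without an arrest exclusion. This is case reporting and not a comparison of arms.
- No section exempts the safety summaries from the population rule.

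**The case against.** The best defence is placement. The sentence stands under the Primary outcome heading, between the primary model and its per-protocol repeat, and it refers to participants with an observed response value. A scope limited to outcome models may have been intended. The article also says that it only summarises a fuller SAP, which may define a safety set. This has weight, and a missing safety set is not the point made here. But the sentence says all analyses, whereas the next paragraph names the primary outcome when it means only that. If the SAP does define a safety set, the article's sentence conflicts with it and still needs correcting.

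It is also fair that harms do not vanish, since individual reporting of related serious events continues. That stands, and it limits the point to the comparative summaries.

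Three stronger readings are tempting but not supported:

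- **That 212 exposed participants are lost.** The 25% counts opened boxes, and Implementation {16c} allows for an opened box whose contents were not used. So 212 is an upper figure. Thrombosis is counted only to death, discharge or 30 days, so the share of events lost may also be well below a quarter.
- **That the rule understates whole-blood cost by a third or distorts the cost-effectiveness ratio.** Excluding arrest participants removes their boxes as well as the participants. With one box each, cost per participant is 636/636 in the reduced set and 848/848 in the full set. The ratio 1/0.75 = 1.33 appears only if all 848 boxes are charged to 636 participants. Boxes are opened in both arms, so no effect on incremental cost is shown. The economic population is left to a separate health economics plan that is not at hand.
- **That thrombosis should carry a stated confidence interval here.** Saying only that it will be summarised is ordinary condensation in an article.

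**Conclusion.** The point holds for the safety summaries. As worded, the population rule removes participants in traumatic cardiac arrest from the by-arm summaries of thrombosis and transfusion reactions, although they are randomised, may be transfused and have their data collected. The size is up to about a quarter of opened-box participants (212 of 848). If all were exposed, the zero-event upper bound per arm widens from 0.70% to 0.94%.

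This rests on three things: the literal scope of the sentence, the 25% planning share, and full exposure. If fewer arrest participants are transfused, the effect shrinks in proportion. The primary analysis and the sample size are unaffected.

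**What to change.** In the population paragraph under Primary outcome, restrict the arrest exclusion to the efficacy analyses. Add to Secondary outcome analysis that thrombosis and transfusion reactions will be summarised by arm in all participants who received any trial component, including those in traumatic cardiac arrest, with the arrest participants also shown separately. Because each box holds a single allocated product, arm and product received should seldom differ, so a by-arm layout is adequate.

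Carry the same wording into the SAP, or check that it is already there. The cost is a change of wording and a few extra tables. No new data are needed, and the primary analysis does not change.
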